### Eligibility and recruitment

Pregnant women who have started prenatal care at the Health Units selected will be identified regarding their eligibility potential through access to the information system of the municipal Health Department (*HygiaWeb*). Those potentially eligible will be approached by the interviewer at the time of the prenatal consultation. Women aged ≥18 years, gestational age (GA) up to 15 weeks and 6 days, pre-gestational body mass index (BMI) between 25.0 and 29.9 kg/m2 will be included. Pregnant women who report previous diabetes (or use of oral hypoglycaemic medication and/or insulin) and use of weight loss medications will be excluded. The original study protocol intended to exclude women in twin pregnancies, however, at the time of screening most of them will not have had access to the first ultrasound result.

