### Outcomes

The primary outcome of the study is adequacy of weight gain. Weight measurements will be performed by trained nutritionists in the first and second study evaluations using a portable digital scale (Tanita®, model HS 302).

The measurement made by the nutritionists up to the 13th GW will be considered as the pre-gestational weight. For the women in the 14th GW included in the study, a value of 0.45 kg will be subtracted from the measured weight and for the women in the 15th GW included in the study a value of 0.91 kg will be subtracted from their measured weight. The results of these calculations will be adopted as an estimate of pre-gestational weight. The weight measured in the second study evaluation, preferably between the 34th and 36th GW, will be considered for the calculation of weight gain, rather than the weight measured at the moment of delivery. These procedures will be adopted due to the limitations regarding the use of self-reported pre-gestational weight and due to the high variability of water retention in the late gestation period, as well as the variability of the gestational age at delivery [28].

Weight data will be obtained from all the prenatal consultations. The mean weekly weight gain will be estimated through the difference between the weight measured in the second evaluation and the first weight recorded in the second trimester of pregnancy, divided by the number of days between the evaluation dates, divided by 7. The women with mean weekly weight gain between 0.23 and 0.33 kg in the second and third trimesters of the pregnancy will be considered to present appropriate weight gain. Insufficient weight gain will be considered for those with a mean weekly weight gain of less than 0.22 kg and excessive weight gain for women with weekly weight gain of more than 0.34 kg [23].

Secondary outcomes will be: mean weekly weight gain, changes in food intake, physical activity and the biochemical profile of the pregnant women (fasting glucose, fasting insulin, total cholesterol and fractions, triglycerides and C-reactive protein), complications in the pregnancy (gestational diabetes mellitus, hypertensive disorders and prematurity), birth weight, neonatal adiposity, weight and length/height of children at 6, 12 and 24 months of age.

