Dietary intake will be assessed at the first and second study evaluations through two 24-h recalls on non-consecutive days in each assessment. The multiple-pass technique, performed by trained nutritionists, will be employed to obtain the recalls [29]. The Nutrition Data System for Research software, developed by the University of Minnesota in the United States, will be used to estimate the nutrients intake. Estimation of the usual diet will be carried out using the Multiple Source Method (MSM), a statistical modeling technique program developed by the European Prospective Investigation into Cancer and Nutrition (EPIC) [30]. The MSM eliminates the need for a high number of replications of the method [31] and has been found to be adequate for estimating the diet of pregnant women [32]. In addition, in the first and second evaluations of the study, the women will respond to a questionnaire on the frequency of the weekly consumption of foods of interest to assess adherence to the nutritional counselling program. The instrument used was adapted from the Surveillance System for Risk and Protection Factors for Chronic Diseases by Telephone Survey (*Sistema de Vigilância de Fatores de Risco e Proteção para Doenças Crônicas por Inquérito Telefônico* - VIGITEL) [33].

The practice of walking for leisure, walking for locomotion, and physical exercise will be assessed in the first and second study evaluations using a questionnaire that includes information on performance and duration in the week prior to the interview, according to the questionnaire adapted from the VIGITEL [33].

Blood samples from the pregnant women will be obtained in the first and second study evaluations after 8–12 h of fasting. Blood collection will be performed by a trained professional of the Health Units, by prior appointment. Fasting serum glucose and insulin levels, total cholesterol, LDL, HDL, triglycerides, and C-reactive protein will be measured. Blood glucose and lipid profile will be determined using enzymatic methods, insulin through the immunofluorometric method, and C-reactive protein using the chemiluminescence method.

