Blood pressure will be measured in both study evaluations with an automatic digital arm blood pressure monitor (OMRON®, model HBP 1100, Omron Health Care Inc.), using the mean of three measurements in each evaluation. Pre-gestational hypertension will be considered if the woman presents blood pressure values greater than 140/90 mmHg in the first study evaluation, or if they report the use of antihypertensive medication at the time of the first study evaluation. Those without pre-gestational hypertension that present changes in blood pressure or are using hypertensive drugs at the time of the second study evaluation will be classified as having gestational hypertension [34].

Data for fasting glucose and at one and 2 hours after 75 g glucose load at the time of gestational diabetes mellitus (GDM) screening will be obtained from the *HygiaWeb* System. For the diagnosis of GDM the criteria proposed by the World Health Organization will be adopted, which require alterations in at least one glycemic value at any time during the pregnancy: from 92 to 125 mg/dL fasting, ≥180 mg/dL 1 h after glucose load or from 153 to 200 mg/dL 2 h after glucose load [35].

The third evaluation of the study will preferably be performed at the time of the Heel Prick Test, between the third to the fifth day of life of the newborn. If this is not possible, the third evaluation will be conducted at the postpartum consultation (maximum 10 days postpartum) or at the first childcare consultation (within 15 days of life). Using a structured questionnaire, the following variables will be obtained: number of prenatal visits to the Health Unit, continuous use of medications during the pregnancy, report of chronic health problems of the puerpera, date and type of delivery, gestational age at delivery, maternal complications (hypertensive disorders and hyperglycaemia), and complications before, during and after the birth concerning the mother and the infant. Anthropometric measurements of the baby at birth will be obtained from the maternity ward discharge form.

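### The GDM outcome window opens before allocation, so any qualifying glucose value already on record at entry would dilute the GDM comparison toward no effect

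*Protocol article*

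**What the plan says.** All references are to the protocol article, Methods/design.

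- **Outcomes** lists GDM among the secondary outcomes: "complications in the pregnancy (gestational diabetes mellitus, hypertensive disorders and prematurity".
- **Outcomes** takes the glucose values from the municipal record system (HygiaWeb): fasting and post-load results "at the time of gestational diabetes mellitus (GDM) screening will be obtained from the" system. No gestational week is given for screening.
- **Outcomes** adopts the World Health Organization criteria, which "require alterations in at least one glycemic value at any time during the pregnancy". The ranges are "from 92 to 125 mg/dL fasting, ≥180 mg/dL 1 h after glucose load or from 153 to 200 mg/dL 2 h" after the load, and any one of them suffices.
- **Eligibility and recruitment** admits women who have begun prenatal care, with "gestational age (GA) up to 15 weeks and 6 days". The only glycaemic exclusion is by report: "Pregnant women who report previous diabetes (or use of oral hypoglycaemic medication and/or insulin) and use of weight loss medications will be excluded".
- **Outcomes**, on the biochemical profile: "Blood samples from the pregnant women will be obtained in the first and second study evaluations", after fasting.
- **Outcomes**, on hypertension, uses the first evaluation to identify women already affected. Only the others can become cases: "Those without pre-gestational hypertension that present changes in blood pressure" or use blood-pressure drugs at the second evaluation.
- The **Fig. 1** legend places counselling after the first evaluation.

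**The concern.** A diagnostic criterion may reasonably span the whole pregnancy. A trial endpoint should count events that the allocated treatment had a chance to prevent. Here the stated window starts with the pregnancy, while allocation can come as late as almost 16 weeks. A woman whose routine record already shows a fasting value in range is eligible, since she need not have reported diabetes. As the definition reads, she would be an event in whichever arm she joins.

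Such cases are expected equally in both arms. They leave the number of prevented cases unchanged but add a common amount to both risks, so a real benefit on GDM looks smaller and is harder to detect. The article applies the new-case principle to hypertension and not to GDM, so two complications on one outcome list follow different logic.

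**Working it through.** The article states no GDM rate, expected effect or power, so there is no figure of its own to reproduce. The calculation shows the direction of the effect and a range for its size.

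**From the article:** a planned sample of 300 with 20% loss. Assuming equal arms, 300 × 0.80 / 2 = 120 analysed per arm.

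**Assumed, because not given:**
- q, the share of women in each arm who already have a qualifying value before allocation: 5% to 20%.
- p0 and p1, the risks of new GDM among the remaining women: 20% in control and 12% in intervention. The true relative risk is 0.60 and the true risk difference is −8.0 points.

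**Formulas when any-time values count:**
- Control risk = q + (1 − q) × p0
- Intervention risk = q + (1 − q) × p1
- Observed risk difference = (1 − q) × (p1 − p0)
- Observed relative risk = [q + (1 − q) × p1] / [q + (1 − q) × p0]

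**Worked case, q = 10%:** control 0.10 + 0.90 × 0.20 = 0.280; intervention 0.10 + 0.90 × 0.12 = 0.208. The relative risk is 0.208 / 0.280 = 0.74 and the difference is −7.2 points.

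Power is for a two-sided 5% test of two proportions. The any-time column uses 120 per arm. The new-case column uses 120 × (1 − q) per arm.

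| q | Control | Intervention | Observed RR | Difference (points) | Power, any time | Power, new cases only (n per arm) |
|---|---|---|---|---|---|---|
| 0% | 20.0% | 12.0% | 0.60 | −8.0 | 39% | 39% (120) |
| 5% | 24.0% | 16.4% | 0.68 | −7.6 | 31% | 38% (114) |
| 10% | 28.0% | 20.8% | 0.74 | −7.2 | 25% | 36% (108) |
| 15% | 32.0% | 25.2% | 0.79 | −6.8 | 21% | 34% (102) |
| 20% | 36.0% | 29.6% | 0.82 | −6.4 | 18% | 33% (96) |

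Restricting to women not already qualifying restores the relative risk of 0.60. It also has more power at every q above zero, despite the smaller number of women.

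**Other assumptions, q = 10%:** with control risk 20%, a true relative risk of 0.50 is seen as 0.68, and 0.70 as 0.81. With control risk 15%, 0.60 is seen as 0.77.

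**Under no true effect,** p1 = p0, so both arms have the same expected risk whatever q is. The any-time comparison therefore remains a valid test.

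**The case against.** The strongest objection is that the article does not say pre-allocation values will be used. Its named source is the set of results at GDM screening, and the any-time phrase describes the diagnostic criteria, not a search of dated records. If every value used comes after allocation, q is zero and there is no dilution. This stands as a limit on size. It does not settle the matter, because no screening week is given and no text closes the window.

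Four stronger readings are tempting, and the article does not support them:

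- *A raised first-evaluation research sample makes a woman a GDM case.* That sample is described for the biochemical profile, a separate outcome. Nothing says that it feeds the GDM classification.
- *The trial would mainly report early-pregnancy prevalence.* This needs more than half of control cases to be early, that is q > p0 / (1 + p0), or 0.20 / 1.20 = 16.7% when p0 is 20%. The article gives no basis for such a share.
- *Early cases could create an apparent effect.* Chance imbalance is ordinary sampling error, which the 5% test already covers.
- *Removing women on the first-evaluation sample cannot bias the comparison.* This is true only of samples drawn before allocation. Blood is taken by appointment, the order of allocation and first evaluation is not stated, and allocation is open.

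Three further points were weighed. Previous diabetes is excluded by report, which partly parallels the hypertension step, but it leaves in women with GDM-range values in the current pregnancy. Any-time GDM in all randomised women is a legitimate intention-to-treat quantity, which is why it is kept as a sensitivity analysis. A condensed article may leave date windows to a fuller document, but this one does state a window, and it is the wrong one for an endpoint.

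**Conclusion.** The point holds in conditional form. The GDM endpoint as written is open to values from before allocation, and nothing sets aside women who already met a criterion. To the extent that the routine records contain such values, the comparison is diluted toward no effect on both the difference and ratio scales.

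The size cannot be derived from the article. Under the assumed rates, a true relative risk of 0.60 appears as 0.68 to 0.82 for 5% to 20% already qualifying, and the dilution is nil if all values used postdate allocation. The trial was sized for weight gain, and in the tabulated scenarios power for GDM is below 40% under either definition. The change therefore mainly improves what is estimated. It does not make GDM a well-powered outcome. Priority is low to moderate.

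**What to change.** State in the analysis plan, for the trial endpoint only and with the diagnostic thresholds unchanged:

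1. A GDM event is a qualifying glucose value dated after allocation, in a woman with no qualifying value dated before allocation.
2. Pre-allocation status comes from dated HygiaWeb values, and from the first-evaluation fasting sample only where it was drawn before allocation.
3. Women with no pre-allocation value stay in the at-risk group in both arms. Some undetected early cases will remain among them, balanced between arms in expectation.
4. Women already qualifying are counted by arm in the baseline table.
5. The any-time result in all randomised women is given as a sensitivity analysis.

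Because removal rests only on information dated before allocation and applies alike to both arms, it preserves the randomised comparison.

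The cost is a few sentences and a date check on values the trial already collects. The downside is a slightly smaller denominator and fewer events.

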### Participants timeline

Figure 1 presents an outline of the sequence of the recruitment, intervention, and evaluation activities of the study participants.

**Fig. 1 Fig1:**
[figure not shown]
Sequence of recruitment, intervention, and evaluation activities of the study participants. * The nutrition counselling will take place after the first evaluation of the study.

### Sample size

The sample size calculation was based on the primary outcome of the study. A 20% difference in the proportion of adequacy of weight gain between the treatment groups is expected [42]. Considering a minimum significance level of 5% (α = 0.05) and a power of 90% (β = 0.1), with a 20% loss during monitoring, a sample of 300 women will be sufficient.

### Allocation

The eligible pregnant women that agree to participate in the study will be randomly allocated to the treatment groups. Randomization will be performed directly using the Research Electronic Data Capture (REDCap) software [43, 44], with a spreadsheet of numbers randomly generated by Microsoft Office Excel. Stratification between the groups will be performed considering the prenatal care Health Unit, which may differ in relation to the quality of the prenatal care offered and the socioeconomic profile of the users. Given the nature of the intervention, both the study participants and the researchers will be aware of the group allocation.

### Data collection methods

The pregnant women of both groups will undergo two evaluations in the Health Units during the pregnancy, at the time of the usual prenatal consultation. The first assessment (baseline) will be conducted prior to the 16th gestational week (GW) and the second assessment will preferably take place between the 34th and 36th GW. The third evaluation of the study comprises the analysis of the mother-child binomial. The approach in the third evaluation of the study will preferably be made at the time of the Heel Prick Test, between the third and fifth day of life of the newborn. If this is not possible, the third evaluation will be conducted at the postpartum consultation (maximum 10 days postpartum) or at the first childcare consultation (within 15 days of life). In addition, secondary data on the puerpera and the newborn will be collected from electronic medical records (*SisprenatalWeb*, *Floresce uma Vida* and *HygiaWeb*).

Study data will be collected and managed using the REDCap electronic data capture tools hosted at the Ribeirão Preto Medical School, University of São Paulo [43, 44]. REDCap is a secure, web-based software platform designed to support data capture for research studies, providing 1) an intuitive interface for validated data capture; 2) audit trails for tracking data manipulation and export procedures; 3) automated export procedures for seamless data downloads to common statistical packages; and 4) procedures for data integration and interoperability with external sources.

### Data management

To ensure the quality of the data collected, the research group will consist of trained nutritionists. A guidance manual has been prepared, prior to data collection, to be used as a protocol for all study procedures. It should be emphasized that the REDCap system [43, 44] has mechanisms called “bounds” that aim to reduce possible errors in the data collection step. In addition, all information collected will be checked by a researcher other than the one that entered the data into the system.

### Statistical analyses

The analyses of this study will follow the intention to treat principles. The homogeneity of the sample at the beginning of the study will be verified using Student’s t-test for independent variables or the Mann-Whitney U test, depending on the data distribution, for the continuous variables; and the X^2^ test for categorical variables. For the continuous variables the delta will be calculated and differences with the baseline will be tested using Student’s t-test for dependent variables or the Wilcoxon test. The impact of the intervention on the proportion of women with appropriate weight gain will be assessed by means of the relative risk and 95%CI adjusted for confounding factors.

The statistical correlation method will be used to investigate the impact of the intervention on neonatal adiposity and birth weight. If there is linearity between the treatment group data and outcomes, linear regression models will be employed, adopting adiposity and birth weight as the dependent variables, adjusted for potential confounders.

The analyses will be conducted using the SPSS® software (version 24) and *p* values < 0.05 will be considered significant.

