An inpatient randomized controlled cross-over trial of ad libitum food intake conducted among American adults evaluated the effect of the consumption of ultra-processed products when compared to diets composed of unprocessed foods. The mean weight gain during the 2 weeks of ultra-processed diet was 0.9 (± 0.3) kg. Conversely, during the 2 weeks exposed to the diet based on unprocessed foods, the individuals lost a mean of 0.9 (± 0.3) kg, confirming the hypothesis of the deleterious effect of the consumption of ultra-processed foods on body weight control [21]. However, the effectiveness of nutritional counselling based on encouraging the consumption of fresh or minimally processed foods for weight control in free living individuals is not known.

Data from a meta-analysis that included 23 randomized controlled trials showed that physical activities interventions in pregnant women can reduce maternal gestational weight gain, especially for those with exercise frequency of three times per week and duration of 30 to 45 min. The practice of physical activity might attenuate insulin resistance and act directly on maternal metabolism, reducing the risk of excessive weight gain [22].

This is a two-armed parallel randomized controlled trial conducted with the aim to evaluate the effectiveness of a nutritional intervention based on encouraging the consumption of minimally processed foods and the practice of physical activity for appropriate weight gain in overweight, adult, pregnant women receiving prenatal care in primary healthcare units of the public health system in a Brazilian city.

The primary outcome of the study is appropriate maternal weight gain. Secondary outcomes are: mean weekly weight gain, changes in dietary intake and physical activity, changes in the biochemical profile of the pregnant women (fasting glucose, fasting insulin, total cholesterol and cholesterol fractions, triglycerides and C-reactive protein), complications in the pregnancy (gestational diabetes mellitus, hypertensive disorders and prematurity), birth weight, neonatal adiposity, and weight and length/height of the children at 6, 12 and 24 months of age.

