## Methods/design

### Study setting

This is a two-armed parallel randomized controlled trial that will be conducted among overweight, pregnant women receiving prenatal care in seven Primary Health Units of Ribeirão Preto, SP, Brazil: Waldemar Barnsley Pessoa (Parque Ribeirão), [name] Sahão (Vila Virgínia), [name] da Costa Moraes (Jardim Presidente Dutra), Adalberto Texeira Andrade (Vila Recreio), Carlos Chagas (Vila Abranches), Rubens Issa Halak (Jardim Juliana) and Dr. Ítalo Baruffi (Castelo Branco). The Primary Health Units were selected according to the high demand for prenatal care and the minimum infrastructure necessary to conduct the study.

The study has been approved by the Research Ethics Committee of the School Health Centre of the Ribeirão Preto Medical School, University of São Paulo. Ribeirão Preto, SP, Brazil, (69,997,717.6.0000.5414, and 97,288,818.0.0000.5414).

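### For diet, physical activity and biochemistry the stated test is change against own baseline, so the stated analysis does not compare the randomised arms on these secondary outcomes

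*Protocol article*

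**What the plan says.** The study is a parallel-group trial: "This is a two-armed parallel randomized controlled trial that will be conducted among overweight, pregnant women" (Study setting). The Outcomes section lists among the secondary outcomes "mean weekly weight gain, changes in food intake, physical activity and the biochemical profile of the pregnant women", and the Background gives the same list. Diet, activity and blood markers are measured at the first and second evaluations. Under Data collection methods, the first is before the 16th gestational week and the second preferably between the 34th and 36th.

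The Statistical analyses section then assigns methods as follows.

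- **Baseline comparability:** "The homogeneity of the sample at the beginning of the study will be verified using Student’s t-test for independent variables or the Mann-Whitney U test".
- **Change in continuous variables:** "the delta will be calculated and differences with the baseline will be tested using" the t-test for dependent samples or the Wilcoxon test.
- **Primary outcome** (proportion with appropriate weight gain): the effect "will be assessed by means of the relative risk and 95%CI adjusted for confounding factors".
- **Neonatal adiposity and birth weight:** "The statistical correlation method will be used to investigate the impact of the intervention on neonatal adiposity and birth weight", followed by linear regression if the relation with treatment group is linear.

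The section opens by committing the analyses to intention to treat. It does not say whether the paired tests are run within each arm or on all women together.

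**The concern.** A paired test against baseline asks whether a variable moved between early and late pregnancy. The trial question is whether it moved differently in women who received the counselling. Glucose, insulin, lipids, diet and activity may all shift over this interval in both arms, so a change from baseline cannot be credited to the intervention.

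Diet and physical activity are the behaviours that the counselling targets. Without a between-arm comparison, the stated analysis cannot show whether counselling altered them, and so cannot help to explain a positive or a null result on weight gain. The randomised control group, which protects against this problem, goes unused for these outcomes.

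Mean weekly weight gain, the first secondary outcome listed, raises a separate point. It is a single rate per woman, computed from the first second-trimester weight to the second evaluation, and it has no baseline value. The paired test cannot serve it, and no other analysis of it as a continuous variable is stated.

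**Working it through.** **1. Which outcome gets which test.** Setting the sentences of the Statistical analyses section beside the outcome list:

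| Outcome | Stated analysis | Compares arms? |
|---|---|---|
| Appropriate weight gain (primary) | Adjusted relative risk, 95% CI | Yes |
| Neonatal adiposity, birth weight | Correlation or linear regression on treatment group | Yes |
| Diet, activity, biochemistry | Paired t-test or Wilcoxon test against baseline | No |
| Mean weekly weight gain (continuous) | None that can be applied | No |

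Running the paired test per arm gives two separate answers about change over time. Running it on all women gives one answer about average change, with arm absent. Neither yields a difference between arms.

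**2. Inputs for the size of the problem.** The plan gives no figure for these outcomes, so there is none to reproduce. From the Sample size section, 300 women with 20% loss leave 300 × 0.8 = 240 evaluable, or 120 per arm if allocation is 1:1 (the ratio is not stated). The 300 itself cannot be reproduced uniquely because the control proportion is not given. It is plausible: 25% versus 45%, two-sided 5%, 90% power needs 118 per arm; 118/0.8 rounds up to 148, which is 296 in total. The point does not depend on it. Further assumptions are two-sided 5% tests, normally distributed changes with equal SD, and the same true change in both arms (no intervention effect).

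**3. Chance that exactly one arm is significant.** Let d be the common change in SD units of change. The power of one within-arm test is approximately

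p = Φ(d√120 − 1.96) + Φ(−d√120 − 1.96)

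and, since the arms are independent, the chance that exactly one is significant is 2p(1 − p).

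| d | p | Exactly one arm, 2p(1 − p) | Both arms, p² |
|---|---|---|---|
| 0 | 0.050 | 9.5% | 0.3% |
| 0.10 | 0.195 | 31% | 3.8% |
| 0.18 | 0.50 | 50% | 25% |
| 0.30 | 0.908 | 17% | 82% |
| 0.50 | about 1.0 | about 0% | about 100% |

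Simulation (20,000 runs each) at d = 0, 0.18, 0.30 and 0.50 gave 9.6%, 50.4%, 17.1% and 0.07%. On the same data a two-sample t-test of the deltas rejected in 5.2%, 4.9%, 4.7% and 5.0%.

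The last row is no reassurance. Discordance vanishes there only because both arms are significant, and that pattern still says nothing about a difference between them.

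**4. What a between-arm test offers.** With 120 per arm, a two-sample comparison of the deltas has power of 34%, 64%, 87% and 97% for differences of 0.2, 0.3, 0.4 and 0.5 SD of change. Adjusting the follow-up value for baseline is more precise. With equal SDs at both evaluations, its variance relative to change scores is (1 − r²)/(2(1 − r)) = (1 + r)/2, where r is the correlation between baseline and follow-up. For assumed r of 0.3, 0.5 and 0.7 this is 0.65, 0.75 and 0.85.

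**The case against.** The strongest reply is that this is a condensed article. It does not say that the paired tests are the only analysis of these outcomes, and a fuller plan might compare the deltas between arms. On that reading the paired tests merely describe change. The text supports this a little: it speaks of the impact of the intervention only for the relative risk and for neonatal adiposity and birth weight, all of which are treatment-group analyses. This does not remove the point. The article is not silent on these outcomes. It names a test for change in continuous variables, names the comparison (with baseline), and gives the two-sample tests another job. That is a method fixed wrongly, which a reader following the protocol would carry out.

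Several stronger readings are tempting, and the documents do not support them.

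- **That the trial compares no continuous outcome between arms.** Birth weight and neonatal adiposity are continuous and do get a treatment-group analysis.
- **That the trialists intend to read significance in one arm only as an effect.** The article states no such rule. It is a foreseeable misuse, not a planned one.
- **That false findings would run at 32-50%.** That range follows from assuming 30-80% power in each arm. The documents give no expected changes or SDs, so the supportable range is about 0-50%, and only under the misuse just described.
- **That the paired test was assigned to mean weekly weight gain.** The natural reading is that no test was assigned. That is an omission, and it is softened because the primary outcome is a categorisation of weekly gain that is compared between arms.

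It is also fair that a two-sample test of the planned deltas would cure the invalidity. Baseline adjustment is the better choice for precision, but it is not the only valid one.

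**Conclusion.** The point holds for dietary intake, physical activity and biochemical profile: as written, the stated test for these secondary outcomes makes no use of the randomised comparison. This follows from the text alone and needs no assumption. Mean weekly weight gain should be settled at the same time, because the paired test cannot serve it.

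The numerical size is conditional. If separate within-arm p-values were compared, exactly one arm would be significant in about 0-50% of cases with no intervention effect, depending on the common change, against 5% for a between-arm test. This rests on 120 evaluable women per arm, 1:1 allocation, two-sided tests and normal changes with equal SD.

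The wording is wrong and should be fixed. It does not threaten the trial's main conclusion: the primary outcome, the sample size built on it, birth weight and neonatal adiposity are not touched.

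**What to change.** In the Statistical analyses section, make the inferential analysis of each continuous outcome measured at both evaluations a between-arm comparison. Fit a linear model of the second-evaluation value on arm, baseline value and Health Unit (the stratification factor named under Allocation), with transformation where the marker is skewed. Report the adjusted difference between arms with its 95% CI. Keep within-arm changes as description only.

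For mean weekly weight gain, fit the same type of model with arm, baseline weight or BMI, and Health Unit.

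The cost is a few sentences of analysis wording. No extra data, visits or participants are needed, and the named software (SPSS) fits these models. The change should be recorded before the arms are compared on these outcomes.
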